### Follow-up and end points

Patients will be followed up using a structured telephone interview on postoperative day 30 and a visit to the trial centre on postoperative day 90. The primary end point for postoperative morbidity will be a composite end point, comprising any rehospitalisation, acute kidney injury (AKI), suspected or proven bacterial infection requiring treatment or acute decompensated HF (ADHF) at postoperative day 90. AKI will be defined according to the Kidney Disease: Improving Global Outcomes criteria [12]. ADHF during the index hospital stay is defined as the new onset or worsening of shortness of breath and signs of congestion, including peripheral oedema, moist rales and radiological signs of congestion or pleural effusion requiring intravenous treatment with diuretics. After discharge, ADHF is defined as the new onset or worsening of shortness of breath requiring intravenous diuretic therapy or rehospitalisation for HF > 24 h.

The secondary end points will include the individual components of the primary end point, mortality, the incidence of myocardial infarction or injury, quality of life and patient satisfaction at postoperative days 30 and 90. A detailed list of the end point definitions is provided in the Supplement. Data transferred to patients’ health insurance providers will be analysed to assess their utilisation of healthcare services after discharge and healthcare-related costs in both treatment arms. Physicians involved throughout the interventions, including anaesthesiologists, cardiologists, surgeons and non-clinical physicians, such as patients’ general practitioners, will receive questionnaires to perform a process evaluation of the intervention, which might help identify the strengths and weaknesses of the process, with the latter to be improved before transfer into routine care.

### Sample size calculation and statistical analyses

The primary end point of this trial has not been used in other studies, and no event rates after 90 days were available for our study cohort. However, overall complication rates between 24.6% and 29.7% have been reported for comparable surgical patient cohorts [13–15]. Therefore, our sample size calculation assumed a 26% event rate. Considering a significance level of 0.05, a two-sided *z*-test (PASS 2020; NCSS, LLC, Kaysville, UT, USA) indicated a sample size of 492 per group to demonstrate an odds ratio of 0.65 in the intervention group with a power of 80%. Considering a dropout rate of 10%, 1094 patients with NT-proBNP levels ≥ 450 pg/mL must be included. Since 37% of the patients evaluated in the pilot study had preoperative NT-proBNP levels ≥ 450 pg/mL, and fewer exclusion criteria were applied, we assumed that 30% of all the included patients would have NT-proBNP levels above the cut-off [11]. Therefore, approximately 3647 patients need to be screened to ensure 547 patients in both the control and intervention groups.

An independent clinical end point adjudication committee will evaluate the primary end point of this trial. All primary and secondary end points will be described using descriptive statistics and compared with t-tests or chi-squared tests, depending on the parameter type. Subsequent outcome analyses will use univariable logistic regression for the primary end point, and multivariable logistic regression will be added to adjust for possible confounding variables. Further analyses will evaluate site-specific effects, and if found, adjustments will be performed.

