### Study population

The study population will comprise patients aged > 65 years with American Society of Anesthesiologists classification II or higher who will undergo elective major non-cardiac surgery under general anaesthesia. Surgical risk will be assessed according to the current 2022 ESC guidelines on the cardiovascular assessment and management of patients undergoing non-cardiac surgery, and only patients with intermediate or high surgical risk will be included [3]. The exclusion criteria include surgery with an approximated duration of less than 30 min, transplant surgery and other criteria that might interfere with the chosen end points. The inclusion and exclusion criteria are summarised in Table 1.

**Table 1 Tab1:** Inclusion and exclusion criteria

Inclusion criteria	Exclusion criteria
Age ≥ 65 years	Incision suture time < 30 min
Elective non-cardiac surgery with intermediate or high surgical risk under general anaesthesia	Surgery with general anaesthesia within the past 30 days
ASA ≥ II	Local or regional anaesthesia without general anaesthesia Surgery involving the kidneys (e.g. nephrectomy, partial kidney resection) Chronic kidney disease with eGFR < 15 ml/min or chronical dialysis Surgery utilising cardiopulmonary bypass Emergency surgery Transplant surgery Participation at another interventional trial Insufficient language skills Lacking capacity to consent of patients under legal supervision

*ASA* American Society of Anesthesiologists, *eGFR* estimated glomerular filtration rate

Patients will be screened when they present for routine preoperative evaluation before the scheduled surgery. After written informed consent to participate in this trial is obtained, the patient’s NT-proBNP will be measured in venous blood using a validated point-of-care immunoassay with a measurement range of 60–9,000 pg/mL (proBNP + , cobas h 232; Roche Holding AG, Basel, Switzerland), which yields a result in approximately 10–12 min. If the NT-proBNP level is < 450 pg/mL, further participation in this trial is precluded, and the patients will undergo routine treatment. If the NT-proBNP level is ≥ 450 pg/mL, the patients will undergo 1:1 block randomisation using a computer-generated list implemented in the electronic case report form into a standard care and an intervention care group.

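### Continuous secondary end points are assigned unadjusted t-tests, although covariates known in both arms before randomisation would allow a modestly more precise analysis

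*Protocol article*

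**What the plan says.** The Protocol article, under Sample size calculation and statistical analyses, covers every end point in one sentence. It opens with "All primary and secondary end points will be described using descriptive statistics" and goes on to say that they will be "compared with t-tests or chi-squared tests, depending on the parameter type".

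Modelling comes next: "Subsequent outcome analyses will use univariable logistic regression for the primary end point, and multivariable logistic regression will be added". Adjustment for centre is conditional: "Further analyses will evaluate site-specific effects, and if found, adjustments will be performed".

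Under Follow-up and end points, most of the secondary list is binary: the components of the composite, mortality, and myocardial infarction or injury. The entries that may be continuous are "quality of life and patient satisfaction at postoperative days 30 and 90".

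Under Study population, "NT-proBNP will be measured in venous blood using a validated point-of-care immunoassay". This is done after consent and before randomisation. Age, ASA class and surgical risk class are inclusion criteria in Table 1, so they too are known before randomisation.

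**The concern.** The article makes a choice here; it is not silent. It names the t-test for continuous end points. The regression it adds is logistic, which cannot serve a continuous score, and the sentence refers only to the primary end point. The authors accept covariate adjustment for the primary end point but give continuous secondary end points none, apart from a site adjustment that depends on the data.

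What is at stake is precision. Part of the spread in a day-30 or day-90 score is usually predictable from patient characteristics at entry. A t-test leaves that part in the error term, whereas a linear model removes it. The treatment estimate remains unbiased with either method.

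**Working it through.** **Inputs from the Protocol article.** 26% event rate, odds ratio 0.65, two-sided alpha 0.05, 80% power, 492 per group, 10% dropout, six centres, 1:1 allocation.

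**The plan's own figure.** Intervention odds = 0.65 × 0.26/0.74 = 0.2284, so the intervention rate is 0.2284/1.2284 = 0.1859. The unpooled formula gives n = (1.960 + 0.842)² × (0.26×0.74 + 0.1859×0.8141)/(0.26 − 0.1859)² = 491.6, so 492 per group. Then 984/0.90 gives 1094. The figure reproduces. It concerns the binary primary end point and is used here only for the number of evaluable patients. The article gives no target difference for a continuous end point.

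**What the t-test can detect.** With 492 per arm and 80% power, the detectable difference is (1.960 + 0.842) × √(2/492) = 0.179 SD.

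**Effect of adjustment.** Let r be the (multiple) correlation between the covariates and the outcome. Residual variance is multiplied by 1 − r², the detectable difference by √(1 − r²), and the equivalent sample size by 1/(1 − r²). The documents give no r, so the table shows a range.

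| Assumed r | Variance cut | Detectable difference (SD) | Power at 0.179 SD | Equivalent n per arm |
|---|---|---|---|---|
| 0 (t-test) | 0% | 0.179 | 80.0% | 492 |
| 0.1 | 1% | 0.178 | 80.4% | 497 |
| 0.2 | 4% | 0.175 | 81.6% | 512 |
| 0.3 | 9% | 0.170 | 83.6% | 541 |
| 0.5 | 25% | 0.155 | 89.9% | 656 |
| 0.6 | 36% | 0.143 | 93.8% | 769 |

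The equivalent sample size rises by 1/0.99 − 1 = 1% at r = 0.1 and by 1/0.91 − 1 = 10% at r = 0.3.

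**Which rows apply.** The covariates known in both arms are restricted by eligibility: NT-proBNP at least 450 pg/mL (assay ceiling 9,000), age at least 65, ASA II or higher, and two surgical risk classes. That tends to lower what they explain, so 0.1 to 0.3 is the cautious range. The rows at 0.5 and 0.6 would need a baseline value of the same scale. The article lists quality of life only at days 30 and 90. PHQ-9 and GAD-7 appear under Intervention and are not stated for controls, so they cannot be counted on as covariates.

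**Cost of the extra terms.** Six centres need 5 terms, and log NT-proBNP, age and surgical risk need 1 each. If ASA class needs 2 (an assumption), the total is 10. The expected variance inflation from estimating them is about (984 − 3)/(984 − 10 − 3) = 981/971 = 1.010, or 1%. At r = 0.1 this roughly cancels the gain. At r = 0.3 the net variance factor is 0.91 × 1.010 = 0.919, so most of the gain remains.

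**The case against.** The strongest reply is that nothing here is wrong. In a 1:1 randomised trial with about 492 evaluable patients per arm, the t-test is a valid comparison. The point touches one or two secondary end points whose scales are not shown, and a satisfaction item analysed as categories would not be t-tested at all. The site sentence is not limited to the primary end point and so may already bring in centre. All of this stands. It limits the point to an optional gain in efficiency, but does not change the fact that the article names an unadjusted test while usable covariates are in hand. A site adjustment made only if an effect is found is also weaker than one fixed in advance.

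Three stronger readings are tempting, and the documents do not support them.

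- **Quality of life compared among survivors only.** A reader might infer this because mortality is a separate end point and a patient who has died gives no score. The article never says that deaths are left out. How they are handled may be set in the SAP, and the article places end point details elsewhere: "A detailed list of the end point definitions is provided in the Supplement". Neither is shown. Under assumed day-90 mortality from 3% v 2% up to 10% v 7%, with the extra survivors 0.5 to 1.0 SD lower, the shift would run from 0.01/0.98 × 0.5 = 0.005 SD to 0.03/0.93 × 1.0 = 0.03 SD. It is zero if no deaths are prevented.
- **Costs compared by t-test.** The insurance-data analysis is described after the secondary list, in its own sentence and with no test named.
- **A large gain, such as a quarter to a third more patients or above.** That would need covariates explaining a fifth or more of the variance, or a baseline quality-of-life score. The article supports neither.

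**Conclusion.** The point holds as a minor improvement. As written, continuous secondary end points get an unadjusted t-test, although centre, NT-proBNP, age, ASA class and surgical risk class are available in both arms before randomisation. The inference is valid, so what is lost is precision. With an assumed r of 0.1 to 0.3, adjustment cuts variance by 1% to 9%, equivalent to about 1% to 10% more patients. At the lower end the cost of the extra terms leaves little or no net gain. A larger benefit depends on a baseline quality-of-life score that the article does not mention. The primary end point and the sample size are unaffected. How deaths enter the quality-of-life analysis is for the SAP to confirm and is not a defect of this text.

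**What to change.** For continuous secondary end points, replace the t-test with linear regression of the score on arm, with these covariates fixed in advance: centre, log NT-proBNP at entry, age, ASA class and surgical risk class. Add the baseline value of the same scale only if it is already recorded in both arms. Report the adjusted mean difference with its 95% confidence interval. For these end points the fixed centre term replaces the rule that adjusts only if a site effect is found.

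The cost is a change of analysis wording, made before the outcome data are seen. It needs no new visits, measurements or patients, and no change to care.

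### One prespecified primary model with centre and baseline covariates would serve better than an unadjusted test with site adjustment only on condition; the gain is modest and depends on how prognostic the covariates are

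*Protocol article*

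**What the plan says.** Everything on this point is in the Protocol article, section Sample size calculation and statistical analyses, except the randomisation, which is under Study population.

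- **Sizing.** The calculation is unadjusted: "Considering a significance level of 0.05, a two-sided" z-test "indicated a sample size of 492 per group to demonstrate an odds ratio of 0.65 in the intervention group with a power of 80" per cent, where "our sample size calculation assumed a 26% event rate".
- **Comparison.** A binary end point is compared by chi-squared test, and the primary end point is then analysed by univariable logistic regression.
- **Adjusted model.** After that, "multivariable logistic regression will be added to adjust for possible confounding variables". The covariates are not named.
- **Centre.** "Further analyses will evaluate site-specific effects, and if found, adjustments will be performed". No criterion for finding an effect is given. The sentence does not say whether it means event rates that differ by site or a treatment effect that differs by site.
- **Allocation.** "1:1 block randomisation using a computer-generated list implemented in the electronic case report form", at six hospitals. The article does not mention stratification by site.

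The order of the sentences makes the unadjusted comparison the natural reading of the main test. No sentence says in terms which result decides the primary hypothesis.

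**The concern.** Three things that the article does fix could be fixed better.

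1. **Reason for adjusting.** Randomisation already deals with confounding at baseline, and any remaining imbalance is chance. Covariates are worth including because they explain outcome variation and so sharpen the treatment comparison. A confounding rationale invites covariates chosen after imbalances are seen.
2. **Site rule.** Whether centre enters depends on the trial's own outcome data. Always including six levels costs five parameters and removes the decision.
3. **Effect measure.** The odds ratio is non-collapsible. An adjusted (conditional) odds ratio lies further from 1 than the marginal one even when arms are perfectly balanced. The planning value of 0.65 is set on marginal rates, so an adjusted odds ratio is not directly comparable with it.

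At stake are a few points of power in a trial planned at 80%, and a clear statement of which estimate answers the hypothesis.

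**Working it through.** **Step 1. Reproduce the plan's figures.** Inputs from the article: control rate 26% (taken as the control-arm rate), odds ratio 0.65, two-sided alpha 0.05, power 80%, dropout 10%, 30% above the NT-proBNP cut-off.

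- Intervention odds = (0.26/0.74) × 0.65 = 0.2284, so p2 = 0.2284/1.2284 = 0.1859.
- n per group (unpooled z-test) = (1.960 + 0.842)² × [0.26 × 0.74 + 0.1859 × 0.8141] / (0.26 − 0.1859)² = 7.849 × 0.3438 / 0.005488 = 491.6, so **492**. The pooled version gives 495.
- 492/0.90 = 546.7, so 547 per group and **1094** in total. 1094/0.30 = 3646.7, so **3647** screened.

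All three figures match, on an unadjusted test.

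**Step 2. Power of an adjusted model at the same size.** Logistic regression was simulated with 984 evaluable patients, 1:1, six sites, and marginal rates held at 26% and 18.59%. The article gives no prognostic strength and no size of site effect, so both are **assumed**: one standard-normal prognostic score with the SDs below on the logit scale, and a site SD of 0.3.

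| Score SD (c-statistic) | Unadjusted | Centre only | Centre + score | Runs |
|---|---|---|---|---|
| 0 (0.50) | 79.5% | 79.9% | 79.9% | 6000 |
| 0.5 (0.64) | 79.7% | 80.3% | 81.9% | 6000 |
| 0.8 (0.70) | 79.5% | 80.0% | 83.5% | 6000 |
| 1.2 (0.78) | 79.6% | 80.4% | 87.9% | 2500 |

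The Monte Carlo standard error is about 0.5 points at 6000 runs (√(0.8 × 0.2/6000)) and 0.8 points at 2500. A second simulation, with the c-statistic taken over covariates plus centre, gave 82%, 84% and 86% at 0.66, 0.72 and 0.75. With a larger site SD of 0.5 and no score, centre moved power from 79.2% to 80.4%.

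**Step 3. Type I error.**
- Each single model, fixed in advance, held close to 5%.
- Claiming success if either the unadjusted or the fully adjusted p-value is below 0.05 gave 5.6% to 6.7% across the settings (6.4% and 6.5% at score SD 0.5 and 0.8, 10,000 runs each).
- Testing for a site effect first and adjusting only if it is found gave about 5.3% in 3000 runs, not distinguishable from 5% (standard error 0.4 points).

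**Step 4. Gap between the two odds ratios.** With marginal rates fixed at an odds ratio of 0.65, the conditional log odds ratio is −0.456 at score SD 0.5 and −0.483 at 0.8. These are conditional odds ratios of 0.63 and 0.62.

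**Step 5. Can the data carry the model?** Expected events are 492 × 0.26 + 492 × 0.1859 = 127.9 + 91.5 = 219. Arm (1), centre (5) and four covariates with one term each make 10 parameters, or about 22 events per parameter.

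**The case against.** The strongest reply is that nothing here is invalid. The article gives a readable order: the chi-squared test matches the z-test used for sizing, univariable regression tests the same contrast, and the adjusted and site analyses come later as additions. An unadjusted primary test with adjusted support is legitimate under 1:1 randomisation, and the article states no site stratification that the analysis would have to reflect. The covariate list may sit in an analysis plan that is not shown. The power gain rests on assumed prognostic strength, and eligibility narrows several candidates (NT-proBNP at least 450 pg/mL, age at least 65, intermediate or high surgical risk only, eGFR below 15 excluded).

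Most of this stands, and it limits the point. A reader might infer three stronger things that the document does not support:

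- **That the plan inflates type I error.** This needs a rule that either p-value may be claimed, and the article states none. If the unadjusted test is the deciding one, there is no inflation.
- **That the conditional site rule is itself harmful.** On the figures above it does almost no damage; it simply gains nothing over always including centre.
- **That the trial is under-sized.** The sample size reproduces and delivers about 80% for the test it was planned on.

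What the reply does not remove is that the article itself ties adjustment to confounding and makes centre conditional on the data. An analysis plan that always included centre would have to depart from that sentence.

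**Conclusion.** The point holds as a recommended improvement, not as an error in the design. One prespecified adjusted model would gain about 2 to 4 points of power at the same sample size if the covariates are moderately prognostic (assumed c-statistic about 0.64 to 0.72), more if they are strong, and nothing if they are uninformative. Nearly all of the gain comes from the covariates. The article gives some reason to expect prognostic value: its pilot study linked raised NT-proBNP to morbidity, including infection, and the Discussion links heart failure with kidney failure, while acute kidney injury is part of the composite. It gives no strength for any covariate in the randomised population, so the size remains an assumption. The benefit for type I error is a safeguard against a choice that the text leaves open, not the correction of a stated rule.

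**What to change.** Replace the analysis sentences with one declared primary analysis:

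- **Model.** Logistic regression of the composite on arm, centre (six levels, always included), log NT-proBNP, age, surgical risk class (intermediate or high) and baseline eGFR. Add known heart failure if it is recorded at baseline; it is not an eligibility criterion in Table 1, so this needs confirming. Fix the list before unblinding and call its purpose precision.
- **NT-proBNP.** State how readings above the assay's upper limit of 9,000 pg/mL enter the model.
- **Effect measure.** Name the target, for example a standardised risk difference and a marginal odds ratio obtained from the model, each with a 95% confidence interval, so that the result can be set beside the planning value of 0.65. If the conditional odds ratio is also shown, label it as such.
- **Supportive results.** Make the chi-squared and univariable results supportive.
- **Centre.** Drop the condition on finding a site effect, and report treatment-by-centre heterogeneity descriptively.

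The sample size stays as it is. The cost is wording before unblinding, with no extra patients or visits. The one small drawback is that the model's own odds ratio is conditional and differs from the marginal 0.65, which is why the target measure has to be stated with it.

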## Discussion

The PeriOP-CARE HF trial will evaluate whether combining systematic preoperative screening using an NT-proBNP-triggered standardised preoperative evaluation with interdisciplinary, multimodal and individually optimised treatment throughout the entire perioperative period will reduce postoperative morbidity in patients aged > 65 years undergoing major surgery with intermediate to high surgical risk according to the current ESC guidelines [3].

We will include a broad spectrum of patients, foremost to be able to detect all potential patients with (unknown) HF since prior studies have shown that a large number of patients undergoing major non-cardiac surgery might suffer from undiagnosed HF, which is detected postoperatively for the first time––when HF-related complications occur [1, 11]. We chose a distinct NT-proBNP cut-off that will be applied to all age groups beyond 65 years. Unfortunately, no specific cut-offs exist for the perioperative period that could have been used. However, the selected cut-off of 450 pg/mL showed good precision in our pilot study, which was conducted before designing the PeriOP-CARE HF trial to select our primary morbidity end point after 30 days. It must be highlighted that the NT-proBNP measurement at the patient’s bedside is a vital part of the new treatment approach that will be evaluated in the PeriOP-CARE HF trial. Since the result will be immediately available, randomisation and preoperative evaluation can be initiated immediately to ensure quick processes leading to a rapid interdisciplinary patient risk discussion by the POM board, and subsequent preoperative optimisation can begin as soon as possible.

To ensure this process, the standardised preoperative evaluation will occur in the anaesthesia outpatient clinic, where all examinations, such as clinical examination, ECG and echocardiography, will be available. It is vitally important to link the elevated NT-proBNP level with potential abnormal ECG and/or echocardiography findings. A relevant number of patients with HF likely suffer from HF with preserved ejection fraction (HFpEF) or atrial fibrillation. Patients with HFpEF are at special risk for postoperative ADHF since 72% of the patients with de novo postoperative ADHF had preserved left ventricular ejection fraction [1]. Patients with atrial fibrillation but not HF might present with elevated NT-proBNP levels comparable to those of patients with HF [16]. However, since perioperative atrial fibrillation is also associated with adverse outcomes after major surgery, the multimodal intervention that will be performed in our trial will be adequate and might improve the outcome for these patients [17].

The POM board has a crucial role in the preoperative optimisation process because all involved specialities will discuss the patients’ individual findings. This discussion will be enriched by the additional expertise and personal knowledge of the patient’s general practitioner. While such a board has never been established in non-cardiac surgery, interdisciplinary conferences, such as tumour boards or the heart teams––which now have a Class I recommendation––have been shown to improve outcomes in other settings through their interdisciplinary decisions [18, 19]. The POM board ensures an individualised decision that is the most suitable and appropriate for the patient and their concomitant diseases. For example, major visceral oncological surgery could not be postponed in a manner an elective knee replacement potentially can. The involved physicians will make all these difficult decisions via consensus to ensure the best possible outcome for the patient.

The intraoperative management of the patients will focus on maintaining optimal haemodynamics, which should help improve patients’ outcomes. Since intraoperative hypotension is strongly associated with adverse outcomes, such as mortality, AKI and myocardial injury, our strategy focuses on avoiding hypotensive episodes [20]. Therefore, we intend to measure arterial pressure continuously from the beginning of anaesthesia induction because many intraoperative hypotension episodes occur during anaesthesia [21]. Consequently, continuous invasive or non-invasive measurement of arterial blood pressure can potentially reduce the incidence and severity of intraoperative hypotension and will, therefore, be performed for all interventional patients participating in the PeriOP-CARE HF trial [22]. Furthermore, patients with HF might be at special risk for volume overload with subsequent congestion in the postoperative period. Therefore, goal-directed therapy will be performed during surgery to ensure optimal oxygen delivery that is guided by fluid boluses, inotropic agents or vasopressors, according to the cardiac stroke volume and dynamic preload parameters.

Goal-directed therapy during non-cardiac surgery has generally been shown to reduce postoperative complications [23, 24]. For example, beneficial effects have been observed concerning mortality, AKI, infective complications and anastomotic leakage after abdominal surgery [25, 26]. However, controversial data have emerged concerning the use of rigid haemodynamic algorithms during major surgery. Especially the goal of maximising cardiac stroke volume and the liberal use of intraoperative dobutamine was not associated with improved outcomes but even adverse effects [27]. Therefore, our trial will use continuous flow monitoring through cardiac stroke volume in all patients and adhere to the current German guidelines on the intraoperative haemodynamic monitoring and management of adults undergoing non-cardiac surgery [28].

The postoperative intervention which is evaluated in the PeriOP-CARE HF trial focuses on the early detection and subsequent treatment of postoperative HF-related complications. This goal is particularly relevant because most postoperative complications occur during the first days after surgery when patients should be under distinct monitoring on the surgical wards. However, HF-related complications might not be the focus of the surgical ward. Therefore, we will perform an interdisciplinary visit to improve the awareness of the surgical ward team for the patients.

In general, HF nurses or nurse practitioners are widely accepted as relevant to improved outcomes in patients with HF [29]. However, they are not currently present on surgical wards, and the PeriOP-CARE HF trial will extend their role to postoperative patients. Furthermore, HF nurses will initiate the patients’ further ambulatory treatment for HF-related issues after discharge, which will be conveyed to their general practitioner before discharge, reducing the period in which a patient’s treatment might be insufficient because the ambulatory physician is unaware of a potential new diagnosis.

The goal of the PeriOP-CARE HF trial is foremost to reducing the postoperative morbidity of the patients receiving the new interdisciplinary treatment approach. Unfortunately, most studies have focused on major adverse cardiovascular events, such as myocardial infarction, stroke and cardiac death. However, we believe these measures do not sufficiently reflect overall risk and, specifically, HF-related complications. Therefore, the primary end point of the PeriOP-CARE HF trial is a composite, including relevant postoperative HF-related morbidity measures. While ADHF is evidently an important end point, any unplanned rehospitalisation during the follow-up period may reflect an additional robust outcome, indicating overall postoperative morbidity. AKI was included in the composite end point because it is generally a frequent postoperative complication that can be reduced by specific interventions. A large proportion of patients develop chronic renal failure after AKI following non-cardiac surgery. Furthermore, the association between HF and chronic or acute kidney failure is well-known [30, 31]. Lastly, any bacterial infection is part of the composite morbidity end point because it represents a specific complication in the postoperative period, and our pilot study revealed a higher incidence in patients with elevated NT-proBNP levels [11]. Interestingly, pneumoniae and other bacterial infections that required antibiotic treatment resulted in an overall increased incidence of any infection. This finding might reflect HF-related limitations in microcirculation and pulmonary congestion, favouring bacterial infection in the lung.

Besides mortality and ischaemic conditions such as myocardial injury and infarction, the secondary end points will focus on the long-term consequences of the interdisciplinary treatment. The proposed intervention will certainly increase the costs of the perioperative treatment, such as the additional point-of-care measurement of NT-proBNP, the POM board and postoperative observation. However, it may provide distinct benefits for both the patient and the healthcare system by reducing the need for procedures (and costs) that might arise from increased long-term postoperative morbidity, such as chronic dialysis. These costs will be examined using health insurance data for the patients included in the PeriOP-CARE HF trial.

Finally, if the intervention evaluated in the PeriOP-CARE HF trial is demonstrated to be beneficial, it could be easily and broadly implemented in the perioperative management of these at-risk patients because most of the hospitals performing surgeries with intermediate to high surgical risk would have already incorporated all the involved specialities. Therefore, implementing the interdisciplinary conference after standardised evaluation is possible. In those hospitals where, for example, no cardiologists are present, telemedicine could be used to bring this expertise to the conference.

In conclusion, the PeriOP-CARE HF trial will evaluate a new interdisciplinary, standardised treatment approach for patients with suspected or known HF to reduce their overall postoperative morbidity. This new treatment approach could potentially reduce not only patients’ morbidity but also healthcare costs. If the PeriOP-CARE HF trial yields positive results, the treatment of patients with HF undergoing major non-cardiac surgery could be considerably improved.

